Eligibility criteria	Include: French individuals diagnosed with CF (sweat chloride >60 mmol/L or a genotype known to cause the disease), aged 6–21 years, with the ability to perform pulmonary function tests with FEV_1_%>40 and the ability to swallow tablets.Individuals were excluded if they had the following: Allergy to macrolide antibiotics Long-term (>3 months) with macrolides during the 12-month period before study entry Liver disease with liver function tests >2 times the laboratory upper limit History of portal hypertension Kidney disease with serum creatinine >150 µmol/L and/or creatinine clearance <50 mL/min Use of any of the following in the 3 months before study entry: DNase, inhaled tobramycin, inhaled steroids	Individuals will be considered for inclusion if they have a clinically confirmed diagnosis of CF (ie, are present in the UK CF Registry) and have an observation date within the recruitment periods defined in section 4.3.1, aged between 6 and 21 years, and obtained FEV_1_%>40 on their pulmonary function test (taken on the day of the annual review). It is assumed that all individuals have the ability to swallow tablets.Exclusion criteria are as follows: Intolerance to macrolide antibiotics recorded at any time during study period. Prescription of chronic oral or prophylactic oral macrolides (including azithromycin) recorded at time 0. Acute liver failure with >3×the upper laboratory limit, INR>2, or not responsive to vitamin K at time 0 Recorded cirrhosis with portal hypertension at time 0. Serum creatinine levels >150 µmol/L at time 0. Prescription of DNase, inhaled tobramycin or inhaled corticosteroids recorded at time 0. No follow-up visit for time 1.	Individuals will be considered for inclusion if they have a clinically confirmed diagnosis of CF (ie, are present in the US CF Registry) and have an observation or encounter date within the time periods defined in section 4.3.1, aged between 6 and 21 years, and obtained FEV_1_%>40 on their pulmonary function test (taken on the day of the encounter visit). It is assumed that all individuals have the ability to swallow tablets.Exclusion criteria are as follows: As in the UK Emulated Trial As in the UK Emulated Trial Non--related liver disease recorded at time 0. Laboratory results from liver tests are not available in the US registry. Recorded cirrhosis at time 0. Portal hypertension is not available in the US registry. As in the UK Emulated Trial As in the UK Emulated Trial As in the UK Emulated Trial

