#### Definition of time 0 and the index visit

Time 0 is defined as the time at which individuals meet the eligibility criteria and ‘enter’ the emulated trial, analogous to the time of randomisation in the target trial. Time 1 is 12 months postbaseline, and the outcome of interest is forced expiratory volume in 1 s (FEV_1_%) at time 1.

For the emulated trials conducted within period p (p=1,2,3), we define an ‘index visit’ for each individual who meets the eligibility criteria during the recruitment period, such that the date of the index visit is time 0. Follow-up visits take place approximately 12 months after the index visit, and an eligibility criterion is that individuals are required to have a follow-up visit. Index visits and follow-up visits are defined differently in the UK and US emulated trials, due to differences in data collection between the two registries. Moreover, the visit we use for treatment, outcome and covariate data at time 0 and time 1 differs between the UK and US emulated trials; figure 1 summarises these differences.

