##### US CF Registry Data

Within the period p, the index visit is defined as the first stable encounter visit at which an individual meets the eligibility criteria in the 2-year recruitment period. The follow-up visit is defined as the date of the stable encounter visit that is closest to 12 months after the index visit, but which falls within 9–15 months after the index visit. Individuals are included in the treatment group if they are recorded as being prescribed treatment at the index visit, as this is often assumed to be the treatment start date. Once an individual starts treatment, we assume they remain on treatment until the follow-up visit. Individuals are included in the control group if they are recorded as not being prescribed azithromycin at the index visit. Controls who are recorded as starting treatment at an encounter visit between the index visit and the follow-up visit are censored at the date of that encounter visit. For the US emulated trials, we also define the prior visit to be the most recent stable encounter visit prior to the index visit.

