### Variables

#### Treatment strategies

The active and comparator treatment strategies used in the target trial are provided in table 2. We aim to match these strategies as closely as possible; however, the target trial specifies doses and frequency of treatment, and this information is not available in the UK or US CF registries.

For both the UK and US emulated trials, the active treatment is prescription of prophylactic oral or chronic oral azithromycin and the comparator is no prescription of prophylactic oral or chronic oral azithromycin.

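### US exclusion 2 is written at time 0, the same visit that defines US treated status, so as worded no treated patient is eligible in either US emulation

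*Protocol article*

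**What the plan says.** Table 2 (Study design) lists as the second UK exclusion: "Prescription of chronic oral or prophylactic oral macrolides (including azithromycin) recorded at time 0". The US list opens: "Exclusion criteria are as follows: As in the UK Emulated Trial As in the UK Emulated Trial Non--related liver disease recorded at time 0". Its second entry therefore takes over the UK macrolide rule as it stands, and the list first departs from the UK at the liver criterion.

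The section defining time 0 sets an index visit for each eligible person, "such that the date of the index visit is time 0". For the US, "the index visit is defined as the first stable encounter visit at which an individual meets the eligibility criteria in the 2-year recruitment period".

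Group membership in the US is read at that visit. "Individuals are included in the treatment group if they are recorded as being prescribed treatment at the index visit", and "Individuals are included in the control group if they are recorded as not being prescribed azithromycin at the index visit". A control who starts azithromycin during follow-up is censored at that encounter and does not move to the treated group.

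Under Treatment strategies, for both registries, "the active treatment is prescription of prophylactic oral or chronic oral azithromycin".

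Two other statements bear on intent. Table 3 explains the 2007 start for the US by the need for a 1-year wash-out, so that people already using azithromycin before entry are not selected. The US section also defines a prior visit, the latest stable encounter before the index visit.

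**The concern.** The macrolide exclusion works in the UK because treatment is read later there: at the follow-up review, or from a prescription date after the index visit in the additional analysis. In the US, treatment is read at the index visit itself. Copying the UK wording across makes one record serve both as a reason for exclusion and as the definition of A=1.

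What is at stake is whether the US contrast can be formed at all from the written rules. With no eligible treated patients, the positivity assumption named under Main analysis fails, the propensity model in equation 3 has no treated outcomes to fit, and the mean outcome under azithromycin cannot be estimated. Whoever builds the US cohort has to depart from the text. In a study whose purpose is to replicate a published trial, that departure should be fixed in the protocol and not left to the programmer.

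**Working it through.** No sample size, power or error rate is involved, so the check is one of logic.

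**The rules side by side (US)**

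1. Eligible at a visit requires no chronic or prophylactic oral macrolide, azithromycin included, recorded at time 0 (Table 2, US column by reference to the UK).
2. Time 0 is the date of the index visit (Definition of time 0 and the index visit).
3. The index visit is the first stable encounter in the recruitment period at which the person is eligible (US CF Registry Data).
4. A=1 requires azithromycin recorded at the index visit (US CF Registry Data).
5. The azithromycin that counts as treatment is of the same chronic or prophylactic oral type that exclusion 2 names (Treatment strategies), so no difference in drug or route separates the rules.

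From 1 to 3, no visit with azithromycin recorded can be an index visit. From 4, A=1 needs exactly such a visit. The intersection is empty. Because later starters are censored as controls, there is no other way into the treated group.

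**Enumeration**

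Take one prior visit and two stable visits in the recruitment period, each with azithromycin recorded (1) or not (0). That gives 2 × 2 × 2 = 8 patterns, written prior–first–second.

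| Reading of exclusion 2 | Treated | Control | Never eligible |
|---|---|---|---|
| At time 0, as written | 0 | 6 | 2 |
| At the visit before the index visit | 3 | 3 | 2 |

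- As written: the four patterns with 0 at the first visit enter there as controls. The two with 1 then 0 enter at the second visit as controls. The two with 1 at both visits never enter. 4 + 2 = 6 controls and 0 treated.
- Read at the preceding visit: 0–1–0, 0–1–1 and 1–0–1 are treated. 0–0–0, 0–0–1 and 1–0–0 are controls. 1–1–0 and 1–1–1 never enter.
- If the 1-year window before the second visit also reaches back to the prior visit, 1–0–1 and 1–0–0 drop out as well. That leaves 3 − 1 = 2 treated, 3 − 1 = 2 controls and 2 + 2 = 4 never eligible.

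These are counts of patterns, not estimates of patient numbers. They show that the arm is empty because the window includes the index visit, and that ending the window before it removes the conflict.

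**Extent**

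Table 3 plans three UK periods and two US periods, 3 + 2 = 5 emulations. Both US ones are affected: 2 of 5.

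**The case against.** The strongest reply is that the intent is plain. Table 3 asks for a 1-year wash-out before entry. The US section treats a record at the index visit as the likely start of treatment and defines a prior visit for the US alone. The target trial itself excluded long-term macrolide use in the 12 months before entry. Together these describe a new-user design, and the US cell in Table 2 looks like shorthand in a summary table. This stands as evidence of intent. It does not amend the exclusion: the wash-out appears only as the reason for the 2007 start, and no sentence says at which US visit exclusion 2 is assessed.

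Figure 1 is not shown, and its caption says it illustrates which visits supply time 0 data. The text describes it as covering treatment, outcome and covariate data and does not name eligibility. Even if it helped, the wording of Table 2 would still need correcting.

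Three stronger readings are tempting, and the documents do not support them:

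- A reader might infer that the US analyses will in fact have no treated patients. An empty arm would show at once when the cohort is built, so it could not silently bias an estimate.
- A reader might infer that two cohorts are equally open, one admitting established users as new starters and one restricted to initiators. The wash-out in Table 3 rules out the first.
- A reader might infer that the rules clash whatever look-back is used. They clash only when the window includes the index visit.

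**Conclusion.** Wrong as written. The US rules for exclusion 2, time 0 and treated status cannot all be applied together, and under the literal text the treated arm is empty in both US emulations, 2 of the 5 planned. The UK emulations are not affected.

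The conclusion rests on the US list in Table 2 following the order of the UK list, which the position of the liver criterion confirms, and on the written text, since Figure 1 could not be seen. The likely cause is a drafting slip, and the document's own wash-out statement points to the intended rule. The correction is therefore narrow, but it should be made before the US cohort is built.

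**What to change.** Reconcile Table 2, Table 3 and the section on US CF Registry Data:

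- In the US column of Table 2, replace the reference to the UK for exclusion 2 with: no chronic or prophylactic oral macrolide, azithromycin included, recorded at any stable encounter in the 1-year wash-out before the index visit, the index visit itself not counted. One year is Table 3's own figure, and stable encounters keep to the rule on usable US visits in the Data sources section.
- Require at least one prior stable visit within that window, so that absence of use is observed and not presumed.
- In the US section, state that azithromycin newly recorded at the index visit is A=1 and no azithromycin record there is A=0.

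The UK column needs no change on this point. The cost is a few lines of protocol wording and the matching cohort code. The downside is that patients with no stable encounter in the year before the index visit leave the US cohort. The documents give no figure from which to estimate how many, so that number should be reported when the cohort is assembled.

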### Setting

#### Time periods

The target trial was conducted from 2001 to 2003, with results published in 2006. Within the data collection period for the target trial, results from other azithromycin RCTs were published,^22^,^24^ after which there was uptake of this treatment in routine clinical practice. We plan to emulate the trial using data from three time periods of 3 years’ duration: 2003–2005, 2007–2009, 2016–2018. Period 1 is close to the timing of the target trial while allowing time for the treatment to have come into use. Periods 2 and 3 were chosen based on features of the data, and ending the time frame in 2018 means that we only use data from the time before CFTR modulators became widespread in clinical practice.

Table 3 provides further details and justification about the three time periods. For each 3-year time period, the first 2 years are used as the ‘recruitment period’, defined as the period during which individuals are considered for inclusion in the emulated trial. The target trial recruited participants over 2 years. Individuals are included in the emulated trial data if they meet the inclusion and exclusion criteria in at least one of their visits during the recruitment period.

**Table 3 T3:** Description of the time periods considered in the UK and US registry data

Time period	Justification for time period	UK data	US data
2003–2005	Closest time period to the target trial, allowing a couple of years for use of azithromycin to uptake in clinical practice.This will only be conducted using the UK data as the US registry did not collect data on azithromycin use during this time.	✓	×
2007–2009	The US registry started collecting data on azithromycin in 2006 and a 1-year wash-out period is required to select individuals who were not taking azithromycin prior to study entry. Therefore, this time period is as close to the time period used in the target trial as is possible for the US registry.	✓	✓
2016–2018	The UK registry started collecting data on treatment prescription dates in 2016. Therefore, this time period is a more recent period that predates widespread use of CFTR modulators but also allows use of treatment date data.	✓	✓

CFTRcystic fibrosis transmembrane conductance regulator

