### US CF registry

The US CF Registry began collecting data on people with CF in the USA in 1986 and is managed by the CF Foundation. It contains longitudinal information on approximately 80% of people with CF in the USA.^19^,^21^

Data are collected on demographic characteristics and on longitudinal variables that change over time. Data collection takes place at ‘encounter visits’ at CF care centres, with data also being abstracted annually. This study will use the encounter visit data which includes relevant information regarding hospitalisations, clinical measurements, medication usage, culture and microbiology, health complications. The encounter visits include routine clinical visits and visits in a hospital or the individual’s home. The non-routine hospital and home intravenous visits may be due to an individual experiencing worsening of their respiratory symptoms, and therefore, their lung function may be unstable at this time. These are referred to as ‘unstable’ visits, whereas routine clinical visits are referred to as ‘stable’ visits. The analyses in this study will use data from the stable visits only.

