#### Covariates

In the target trial, individuals were randomly allocated to the treatment or placebo strategy. In the emulated trials, there is no randomisation. The data on treatment use within the UK and US CF Registries reflects treatment decisions made based on clinical indication and on clinician and patient preference. Being prescribed azithromycin is, therefore, assumed to be informed by a number of factors, many of which are also associated with the outcomes of interest. The association between prescription of azithromycin and FEV_1_% (and secondary outcomes) is, therefore, believed to be confounded by the following factors: age, number of days on intravenous antibiotics (intravenous days), non-intravenous hospital admissions, presence of *Pseudomonas aeruginosa*, *Staphylococcus aureus* or Nontuberculous Mycobacteria, pancreatic insufficiency, CF-related diabetes (CFRD), use of hypertonic saline or inhaled antibiotics and rate of decline in FEV_1_%, BMI z-score and FEV_1_%. These are depicted in a directed acyclic graph in figure 2.

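### The 2016–2018 emulations end before CFTR modulators were widespread but have no rule for people who were already using or starting them

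*Protocol article*

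**What the plan says.** CFTR modulators are mentioned only under Time periods. The text explains that ending in 2018 means "we only use data from the time before CFTR modulators became widespread in clinical practice". The 2016–2018 row of Table 3 describes "this time period is a more recent period that predates widespread use of CFTR modulators but also allows use of treatment date data", and its opening reason for the period is that "The UK registry started collecting data on treatment prescription dates in 2016". That row is ticked for both registries.

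Co-treatments are handled in two other places. Table 2 closes the UK exclusion list with "Prescription of DNase, inhaled tobramycin or inhaled corticosteroids recorded at time 0. No follow-up visit for time 1", and the US list adopts the same items. The Covariates section lists the assumed confounders. The chronic treatments among them are "use of hypertonic saline or inhaled antibiotics". The Notation section defines C as that list together with Figure 2, and the Data analysis section applies one plan to both registries with no covariate specific to a period.

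On data, the UK registry section says that prescribed treatments and CFTR genotype are recorded. The US section lists "medication usage, culture and microbiology, health complications" among the encounter data. Neither names modulators.

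**The concern.** The plan regards modulators as important enough to fix the end of the data window, but it deals with them only by calendar date. Anyone who used a modulator in 2016–2018 stays in the analysis, in whichever azithromycin group they fall.

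A modulator user or starter may show a change in lung function that is not due to azithromycin. If that happens more often in one group than the other, given C, the difference is attributed to azithromycin. Three analyses are exposed: the UK main analysis of 2016–2018, the UK prescription-date analysis and the US analysis of 2016–2018. The results are then judged against the target trial partly on direction and statistical significance. The Sample size section expects far more people than the target trial's 82, so a modest bias could weigh more against a smaller standard error.

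**Working it through.** The article has no figure to reproduce on this point. The check has two parts: where a modulator rule could sit, and how large a bias could be on stated assumptions.

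**Where a rule could sit**

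- Eligibility (Table 2; Inclusion and exclusion criteria): DNase, inhaled tobramycin, inhaled corticosteroids and macrolides are covered. Modulators are not, in either registry.
- Adjustment set (Covariates; Figure 2 legend; Notation): hypertonic saline and inhaled antibiotics are included. Modulators and CFTR genotype are not. Figure 2 itself is not shown, but the text says that it depicts the listed factors and its legend names no modulator.
- Treatment changes during follow-up (US CF Registry Data): the only censoring rule is for US controls who start azithromycin.
- Sensitivity analyses: E-values and repeated entry. The E-values are framed for factors that the registries do not capture.
- Limitations (Differences in the study populations): a general remark that later years may differ in clinical setting, and a plan to compare periods. Modulators are not named.

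The exclusion and confounder lists are written as complete, so this is more than detail left to a fuller document.

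**Two routes to bias**

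1. Use already established at time 0. Benefit gained before time 0 is already in baseline FEV1%, and recent decline and BMI z-score are also in C. What remains is any further effect on the 12-month value.
2. Starts after time 0. Baseline covariates do not capture these, so the full effect could apply. In the UK prescription-date analysis, treated people have time 0 at their first azithromycin date after the index visit, while controls have it at the index visit. For the same index date, treated follow-up therefore begins later in calendar time. If modulator uptake was rising, exposure could differ between arms even if modulator prescribing were unrelated to azithromycin.

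**Illustrative size**

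Bias in the ATE = (modulator effect on FEV1% at 12 months, given C) × (difference in modulator use between arms, given C).

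Both inputs are assumptions, since the article gives neither.

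| Effect (FEV1% points) | 2 percentage points | 5 percentage points | 10 percentage points |
|---|---|---|---|
| 3 | 3 × 0.02 = 0.06 | 3 × 0.05 = 0.15 | 3 × 0.10 = 0.30 |
| 5 | 5 × 0.02 = 0.10 | 5 × 0.05 = 0.25 | 5 × 0.10 = 0.50 |
| 10 | 10 × 0.02 = 0.20 | 10 × 0.05 = 0.50 | 10 × 0.10 = 1.0 |

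The sign follows the arm with more users. A zero difference given C gives zero bias. The larger effects are relevant mainly to recent starters. For established users they overstate the problem, for the reason given under route 1.

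**The case against.** The best defence is that the plan already has a mitigation, the 2018 cut-off, and that nothing in the article shows material use or imbalance. That is right as far as it goes: every entry in the table is assumed, and none is evidence that the bias matters. It is also true that baseline FEV1%, its recent decline and BMI z-score absorb part of the effect in established users. Only two of the five registry-period emulations in Table 3 are affected, plus the supplementary UK analysis. Comparing periods might show an anomaly in period 3, although it could not attribute it to modulators.

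A reader might also infer that 2016–2018 was chosen in order to avoid modulators. The article does not say so. It says that periods 2 and 3 follow features of the data, and Table 3 leads with the start of UK prescription dates. Modulators explain the end year only.

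Two practical objections stand. The article does not say that modulators or their start dates are recorded; it speaks only of treatments and medication in general. And censoring at a modulator start departs from the stated estimand, which contrasts azithromycin with no azithromycin and sets no condition on co-treatment.

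What the defence does not explain is why a co-treatment that sets the end of the data window is handled less strictly than hypertonic saline or DNase. E-values do not fill the gap if the registries do hold the variable.

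**Conclusion.** The point stands as an unhandled co-treatment in the 2016–2018 emulations, and it is worth correcting because the correction is cheap. It is not a demonstrated bias, and the plan does not contradict itself: data from before widespread use can still include some users. A reader might conclude that the period-3 results will be biased by up to a full FEV1% point. The article does not support that, because it gives no prevalence, effect or imbalance. The illustrative range of 0.06 to 1.0 points depends wholly on assumed inputs and falls to zero if modulator use is balanced given C. The conclusion assumes some modulator use in 2016–2018, which the wording allows but does not quantify. The 2003–2005 and 2007–2009 emulations are outside the point.

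**What to change.** Where the registries record modulators, for 2016–2018 only:

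1. Exclude from the analysis set people with a modulator prescription recorded at or before time 0, or add that indicator to C. For the prescription-date analysis, state which date the rule uses in each arm, since time 0 is defined differently for treated and control people.
2. Report modulator use at time 0 and starts during follow-up, by arm.
3. Add a sensitivity analysis for starts during follow-up, for example censoring at modulator start with censoring weights. State that it targets a different estimand, the azithromycin contrast with no modulator start during follow-up, and keep it separate from the main analysis. Its feasibility in the UK data depends on start dates and on covariates that are updated only about once a year.

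If modulators are not recorded, say so and name them in the Limitations section. The cost is some loss of sample in one period (the article gives no basis for saying how much) and one extra analysis. The earlier periods and patient care are unaffected.
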